## **8. OUTCOME DATA**

### **8.1 Definition and Calculation of Outcome Measures**

#### **8.1.1 Primary Outcome – Phase 1b**

The primary outcome measure is the number of patients with severe or very severe treated skin site reactions as determined by the Modified Draize score. The Modified Draize score is defined in the trial Protocol V2.1 26th August 2015.

Modified Draize is collected at the end of treatment. Any score of 4 or 5 categorises the patient as having a severe reaction.

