#### **Primary objective:**

To determine the safety of CT327 application in CYLD mutation carriers

A phase 1b open label clinical trial will be conducted to determine the safety of applying CT327 for four weeks to a single tumour in a CYLD mutation carrier that is scheduled for a routine lesion excision in 8 patients (detailed in section 8.1. below). The treated site will be clinically assessed using a modified version of the Draize score test for signs of local site reaction (See Appendix A). This is a measure of skin inflammation. The lack of any unexpected trial related adverse site reactions, as indicated by a modified Draize score of 3 or below, over 4 weeks of treatment in 5 out of 8 or more patients treated will allow progress to begin recruitment of patients into cohort 2.

### 6.2 Cohort 2

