#### 8.1.1 Cohort 1: Outcome measures

|                             |                                                                                                                                                                                                                                                                                                                                                                           |
|-----------------------------|---------------------------------------------------------------------------------------------------------------------------------------------------------------------------------------------------------------------------------------------------------------------------------------------------------------------------------------------------------------------------|
| Primary Outcome Measure:    | Number of severe treated skin site reactions defined as a Modified Draize score of 4 or above after 4 weeks of treatment (Appendix A)                                                                                                                                                                                                                                     |
| Secondary Outcome Measures: | 

a. Patient reported QoL tools (EQ5D, DLQI)

b. Patient acceptability of trial treatment according to patient treatment questionnaire (Appendix B).

c. Adverse events within a planned 4 week treatment period

d. Compliance as reported in the patient diary, including reasons for non-compliance

 |

The decision to progress from cohort 1 to cohort 2 will be based on the number of severe skin reactions reported and on recommendations from the trial DMC.

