### ***Visit 3a – Week – 4 End of treatment***

Visit 3 will take place at the end of treatment 4 weeks (day 28 +3days) after the entry to trial.

- Pregnancy Test (urine) , for women of child bearing potential only
- Patient treatment questionnaire
- Adverse Events
- Concomitant Medication
- Trial medication returned
- Collect completed Patient Diary

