## **14.3 Decision Criteria**

### **Cohort 1**

We anticipate recruiting 8 patients to cohort 1. It will be acceptable to move to cohort 2 as long as any unexpected treatment related adverse events are experienced in no more than 3 patients.

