### **15.2 Withdrawal of participants**

Trial drug must be discontinued if:

- The participant decides they no longer wish to continue
- Cessation of trial drug is recommended by the investigator
- Pregnancy
- Any significant medical condition (in the judgement of the site investigator)
- Localised reactions:

Any patient reporting treatment site reactions will be assessed in the clinic. A modified Draize score of 4 or above would result in discontinuation of the drug. In the event of such an adverse reaction, blinding may need to be broken to determine if the reaction is related to the application of the trial drug to the treated site. Once the blind is broken, the trial drug will need to be discontinued if it is found to be responsible for the adverse event.

- Systemic reactions:

Any other reported side effects/adverse events that the patient experiences during the trial will be assessed by the chief investigator. If clinically appropriate, the patient will be reviewed in clinic and a decision made regarding discontinuing the trial drug if it is feasible that this is related to the trial drug.

Participants have the right to completely withdraw from the trial at any time for any reason, and without giving a reason. The investigator also has the right to withdraw patients from the trial drug in the event of inter-current illness, adverse events, serious adverse events, suspected unexpected serious adverse reactions, protocol violations, cure, administrative reasons or other reasons. It is understood by all concerned that an excessive rate of withdrawals can render the trial uninterpretable; therefore, unnecessary withdrawal of patients should be avoided. Should a patient decide to withdraw from the trial, all efforts will be made to report the reason for withdrawal as thoroughly as possible. Should a patient withdraw from trial drug only, efforts will be made to continue to obtain follow-up data, with the permission of the patient.

Participants who wish to withdraw from trial medication will be asked to confirm whether they are still willing to provide the following.

- 'end of trial data' as per visit 3 (4 weeks) in cohort 1 or visit 4 (12 weeks) in cohort 2, at the point of withdrawal

- If participants agree to the above, they will be asked to complete a confirmation of withdrawal form to document their decision.

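### The cohort 1 safety outcome does not say which Draize score counts when a patient is stopped early, and the progression rule counts different events in different sections

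*Combined protocol and SAP*

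**What the plan says.** **Scoring time.** The cohort 1 outcome table (protocol section 7, under the heading numbered 8.1.1) gives the primary outcome as "Number of severe treated skin site reactions defined as a Modified Draize score of 4 or above after 4 weeks of treatment". SAP 8.1.1 says "Modified Draize is collected at the end of treatment" and then "Any score of 4 or 5 categorises the patient as having a severe reaction". The only visit between baseline and surgery is Visit 3a in protocol 13.4: "Visit 3 will take place at the end of treatment 4 weeks (day 28 +3days) after the entry to trial".

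**Stopping.** Protocol 15.2 has any patient who reports a site reaction assessed in clinic, and "A modified Draize score of 4 or above would result in discontinuation of the drug". The same section keeps early stoppers in follow-up and analysis if they agree. It also asks patients who want to come off trial medication whether they will give their visit 3 data when they withdraw.

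**Progression.** There are three statements.
- Protocol 6.1 looks for the absence of unexpected trial-related reactions at the site, "as indicated by a modified Draize score of 3 or below, over 4 weeks of treatment in 5 out of 8 or more patients".
- Protocol 14.2 and 14.3 allow the move to cohort 2 "as long as any unexpected treatment related adverse events are experienced in no more than 3 patients".
- The cohort 1 outcome section and SAP 8.4 use the number of severe skin reactions with DMC advice and give no threshold. SAP 8.4 then points to the protocol's statistics section, which counts the unexpected adverse events.

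**The concern.** The stop rule acts on the same score, at the same cut-off, as the primary outcome, but at any time. The outcome has a single planned reading. The patients most likely to reach the cut-off early are therefore the ones taken off drug before that reading, with time for the skin to settle. If the later score is used, an endpoint meant to detect severe local reactions can miss them. The error runs one way: an uncounted reaction can only make progression more likely, and progression opens 12 weeks of exposure in cohort 2.

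The second issue is separate. If the sections that govern progression do not count the same event, the trial has no single pre-specified rule, and the same eight patients could support either decision.

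**Working it through.** **1. Thresholds.** Protocol 6.1 needs at least 5 of 8 patients at Draize 3 or below, so it tolerates 8 − 5 = 3 patients above 3. Protocol 14.2 and 14.3 tolerate 3 patients. The number agrees; the event does not. Cohort 1 has no power calculation to reproduce: 14.2 justifies the 8 patients as feasible and pragmatic.

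**2. One hypothetical patient read against each section.** Suppose a score of 4 at an unscheduled clinic review in week 2, drug stopped, and a score of 2 at day 28.
- Cohort 1 outcome table, scoring after 4 weeks of treatment: read as a week-4 score, no event.
- SAP 8.1.1, end of treatment: no event if this means the day-28 visit; an event if it means the actual stop date, or if any score on record counts.
- Protocol 6.1, judged over the 4 weeks: an event.

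Protocol 13.4 places the end of treatment at week 4. SAP section 6 speaks of patients who withdraw from drug before the end of treatment visit. Both lean towards the scheduled visit, but neither settles the matter.

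**3. Whether the score at withdrawal is secured.** The request for visit 3 data in 15.2 depends on the patient's willingness. It is addressed to patients who wish to come off medication, not expressly to those stopped under the Draize rule. It refers to the visit 3 data set, and neither the Visit 3a list (13.4) nor the cohort 1 schedule (13.7) contains a Draize score. Protocol 14.1 bases the analysis on all patients recruited, so a stopped patient without a score stays in the denominator, and nothing says how that patient is counted.

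**4. Size.** One patient is 1/8 = 12.5 percentage points. Let p be the true share of patients with a severe reaction and c the share of those reactions still captured at scoring. Both are assumptions; the documents give neither. The number counted is X ~ Binomial(8, q) with q = p × c, and

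P(X ≤ 3) = Σ (k = 0 to 3) C(8, k) q^k (1 − q)^(8 − k).

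For p = 0.4 and c = 1: 0.0168 + 0.0896 + 0.2090 + 0.2787 = 0.594.

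| True rate p | c = 1 | c = 0.75 | c = 0.5 |
|---|---|---|---|
| 20% | 0.944 | 0.979 | 0.995 |
| 40% | 0.594 | 0.806 | 0.944 |
| 50% | 0.363 | 0.651 | 0.886 |

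**5. Whether the progression rules can disagree.** Take eight patients who all score Draize 0–3, four of whom have an unexpected, treatment-related adverse event away from the treated site. Protocol 6.1: 8 of 8 at 3 or below, so progress. Protocol 14.2/14.3: 4 patients exceeds 3, so the condition is not met. The severe-reaction wording in the outcome section and SAP 8.4 gives a count of 0 with no threshold to compare it with.

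**The case against.** A reader might infer that an early severe reactor is always counted as no event. The documents do not support that. End of treatment can mean the stop date, SAP 8.1.1 counts any score of 4 or 5, 15.2 asks for data at the point of withdrawal, and 6.1 speaks of the whole 4 weeks. On that reading the score is captured. This stands: the defect is an undefined scoring time, not a certain loss.

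Early reactions also have a second route. SAP section 7 tabulates adverse events from start of treatment to excision, and the DMC reviews cohort 1 safety and advises on progression. This stands in part. Adverse events are graded by disruption of daily activities (protocol 17.1), so a Draize 4 lesion need not be recorded as severe, and the primary outcome itself is not repaired by this route.

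A reader might also infer that four Draize 4 reactions judged expected would fail 6.1 yet pass 14.3. That cannot be shown. Section 6.1 itself speaks of unexpected reactions, 17.1 makes severity part of expectedness, and the deciding source is the Investigator's Brochure, which is not available here. The example in step 5 of the working does not depend on it.

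On size, the protocol anticipates few treatment-related events. At the 3% application site reaction rate listed in 17.2 (any severity, other populations), four or more of 8 has a probability of about 0.00005. Where severe reactions are rare, the gap hardly alters the go decision, though it still affects the reported count.

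**Conclusion.** The point holds as an ambiguity with a one-sided risk. The plan does not say whether scores from unscheduled or stopping visits enter the cohort 1 primary outcome, and the withdrawal clause protects only partly. A severe early reaction can go uncounted, and each one lowers the reported rate by 12.5 percentage points. The effect on the chance of progressing rests on assumed values of p and c: at p = 40% it rises from 0.59 to 0.81 or 0.94 as capture falls to 75% or 50%, and at p = 20% it hardly moves (0.944 to at most 0.995).

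The mismatch in the progression event needs no such assumption. Protocol 6.1 and 14.2/14.3 apply one limit to two events, and SAP 8.4 names a third wording while citing the section that uses the second. The passages must be reconciled. The documents do not show that a wrong decision was taken.

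**What to change.** - **Outcome.** In SAP 8.1.1 and the cohort 1 outcome table, define the outcome per patient as the worst Modified Draize score at any assessment from first application to excision, including unscheduled and stopping visits. This also settles whether reactions (outcome table) or patients (protocol 4.1, 14.1 and SAP 8.1.1) are counted.
- **Missing scores.** State how a stopped patient without a score is counted.
- **Data capture.** List the Draize score in protocol 13.4 (Visit 3a) and 13.7, and on the form used for unscheduled reviews.
- **Progression.** Reconcile protocol 6.1, the cohort 1 outcome section, 14.2, 14.3 and SAP 8.4 to one stated event. Which event governs is for the sponsor and DMC.
- **If cohort 1 is complete.** This is likely: SAP section 2 planned the DMC review for 29/05/15 and protocol version 3.0 is dated May 2016. In that case, report the worst-score count from clinic and adverse event records beside the planned count, labelled post hoc, and do not replace the planned outcome.

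The cost is wording in both documents, one data field and, if cohort 1 has finished, a record check for 8 patients. No visits are added.

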#### **8.1.2 Primary Outcome – Phase 2a**

The primary outcome measure is the proportion of tumours responding to treatment by 12 weeks. According to WHO-RECIST criteria, a reduction in 30% volume would be sufficient to classify a "response" to treatment in oncology. In Phase 2a we will use this criteria as a benchmark when determining a response in this patient population at 12 weeks.

Tumour volume will be measured on the predetermined identified tumours in each patient prior to randomisation and measured again and recorded on the same tumours at 4 and 12 weeks. We will have measures of surface area, height and volume taken 3 times at each visit for each tumour. The mean of each set of 3 measurements will be used to determine the percentage change in volume for each tumour to be able to classify tumours as having a response to treatment or not at each time point (Appendix 3).

#### **8.1.2 Secondary Outcomes**

##### **Patient Reported Measures**

Phase 1b patients will fill in questions 1-4 of the patient treatment questionnaire only, Phase 2a patients will also complete question 5. This is to determine the acceptability of the treatment. This is completed at the final visit, at the end of treatment.

EQ-5D-3L is collected at the baseline visit for both Phase 1b and Phase 2a. The EQ-5D-3L descriptive system comprises the following 5 dimensions: mobility, self-care, usual activities, pain/discomfort and anxiety/depression. Each dimension has 3 levels: no Descriptive problems, some problems, extreme problems. A variable will be derived to describe the unique health of each participant this state is defined by combining 1 level from each of the 5 dimensions. Detailed descriptions regarding calculation of scores can be found in the user guide found at <http://www.euroqol.org>

The Dermatology Life Quality Index (DLQI) questionnaire is designed for use in adults, i.e. patients over the age of 16 and is a patient reported questionnaire. It is collected at the baseline visit. The DLQI is calculated by summing the score of each question resulting in a maximum of 30 and a minimum of 0. The higher the score, the more quality of life is impaired. The DLQI can also be expressed as a percentage of the maximum possible score of 30. Detailed description of the calculation of the DLQI can be found in the instructions for use on the Cardiff University website. <http://www.cardiff.ac.uk/dermatology/quality-of-life>

For phase 2a only there are further secondary outcomes of pain assessment. A substantial amendment (Ref: 151395/806479/32/140/42817) was submitted to the MHRA and REC on the 25th June 2015 for the inclusion of the pain assessment forms to phase 2a. Patients were asked at baseline about any pain in existing tumours. At subsequent visits they were asked if the pain had changed and if there were any new painful tumours.

## **8.2 Analyses of Outcome Data**

### **8.2.1 Analysis of the primary outcome measure: Phase 1b**

The number of unique patients with severe reactions will be reported. The primary outcome will be reported as the number of patients with severe reaction in the Phase 1b trial set (and % of patients with associated 95% confidence interval) with a Modified Draize score of 4 or 5.

In addition, median (IQR) Modified Draize scores will be reported.

### **8.2.2 Analysis of the primary outcome measure: Phase 2a**

The analysis set is the Phase 2a trial set.

#### **8.2.2.1. Descriptive analysis**

Tumour volumes (mean of the three readings) will be reported descriptively as mean (standard deviation) at baseline by treatment group and overall. Tumour-level change in volume at 4 and 12 weeks will be reported as mean percentage change (with 95% Confidence interval) by randomised treatment group. Graphical representation of percentage change in tumour volume from baseline to 12 weeks will be in the form of a waterfall plot (Appendix 3).

In order to assess the possibility of differing percentage changes being influenced by initial tumour size, the mean percentage change from baseline to 4 weeks and baseline to 12 weeks will be reported by baseline tumour diameter categories. Categories will be determined by quartile measurements of baseline tumour diameter.

Mean volume and mean percentage change will be displayed graphically by treatment group and by baseline tumour diameter category.

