| Primary outcome:       | The proportion of tumours responding to treatment by 12 weeks.                                                                                                                                                                                                                                                                                                                                                                                                                                                                                                                                                                                                                                                                                                                                                                                                                                   |
| Secondary outcomes:    | 

a. Change in tumour volume from baseline (pre-randomisation) to 12 weeks

b. Adverse events within a planned 12-week treatment period

c. Compliance including reasons for non-compliance

d. Confirmation of the definition of response (currently according to WHO RECIST criteria where response is defined as >30% reduction in tumour volume, this will be used as a benchmark).

e. Expression of targets of TRK signalling in tumour biopsies as determined by QPCR and immunohistochemistry.

f. Patient reported quality of life using patient reported QoL tools (EQ5D, DLQI)

g. Assessment of acceptability of trial treatment according to patient treatment questionnaire (Appendix B).

h. Patient reported pain using the Patient Pain Assessment Form at 0, 4 and 12 weeks.

 |

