#### **2.1.2 Cohort 2**

All tumours will contribute to the analysis based on the total number randomised (intention to treat population). A secondary analysis will be reported based on the number of tumours which have been treated for 12 weeks (per protocol population).

The primary outcome measure is the number of tumours responding to treatment by 12 weeks reported as a proportion of the number of tumours randomised in the actively and placebo groups separately.

According to WHO-RECIST criteria, a reduction in 30% volume would be sufficient to classify a 'response' to treatment in oncology. In this trial we will use this criteria as a bench mark when determining a response in this patient population. As such one of the outcomes will be to consider and confirm a definition of 'response' to treatment in this group of patients. Tumour volume will be measured on 8 - 10 predetermined identified tumours in each patient prior to randomisation (baseline) and measured again on the same tumours at 4 and 12 weeks. The change in volume for each tumour will be recorded and classified as either having a response to treatment or not.

As an early phase trial, statistical analysis will be exploratory (not based on hypothesis testing) and will be based on descriptive data presented by treatment group. Continuous measurements (including change in tumour volume from baseline) will be summarised and reported as medians and ranges (inter-quartile ranges). Categorical data (including proportions of tumours with adverse events and outcomes from the Pain Assessment Forms) will be summarised and reported as percentages and confidence intervals (95%). Since multiple tumours are sited in individual patients, a secondary analysis based on a multi-level

modelling approach will be undertaken to investigate the relationship between any change in volume and randomised treatment accounting for the multi-level nature of the tumour measurements.

QoL tools (EQ5D, DLQ) will be scored according to scoring manuals and actual scores will be reported descriptively.

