### **Cohort 2**

It is anticipated that 75 tumours could be measured in each treatment arm (150 tumours in total). Tumours receiving placebo treatment are not expected to respond to treatment, set to be very small at 5% ( $p_0$ ). This is the first exploratory trial and as such the design parameters are provided as an exemplar of the size of errors that may be anticipated with these patient numbers.

Using Fleming A'Herns early phase methodology (Fleming 1982, Ahern, 2001) any response on the experimental treatment  $<5\%$  ( $p_0$ ) would not indicate a treatment worthy of further investigation. 75 tumours recruited in the experimental arm would provide evidence of a minimum level of efficacy of approximately 15% ( $p_1$ ), indicating that a level of efficacy of  $>15\%$  would warrant further investigation, with associated error levels of 3.4% type I error ( $\alpha$ ) and 10.8% type II error ( $\beta$ ). This level of efficacy seems clinically plausible and relevant given that there is no current treatment in use for these patients.

The justification to investigate CT327 further is based on observing a minimum number of responses, referred to as the critical number (specified in the Statistical Analysis Plan). The trial will recruit an equal number of placebo-treated tumours to provide an unbiased benchmark.

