## 8.4 Decision Criteria

The decision to progress from Phase 1b to Phase 2a will be based on the number of severe skin reactions reported, with guidance and recommendations from the trial DMC, as reported in the statistics section of the trial protocol and trial master file.

Decision criteria at the end of Phase 2a are predominantly based on the response rate and critical number of responses observed in the treatment group, according to the Fleming A’Hern design. Tumours receiving placebo treatment are not expected to respond to treatment. Using Fleming A’Herns early phase methodology (Fleming 1982, Ahern 2001) any response on the experimental treatment <5% would not indicate a treatment worthy of further investigation. The justification to investigate CT327 further is based on observing a minimum number of responses referred to as the critical number as specified in the document entitled “Critical Number” which is located in the Statistical Trial Master File.

The benchmark for the definition of ‘response’ was set as 30% reduction in tumour volume given the WHO RECIST oncology criteria. As specified in the protocol, consideration will be given to shifts in this criteria, to smaller reductions in volume, to observe the impact on the response rate and Fleming A’Hern critical number in the treatment group, as outlined in 8.3 above. The reasoning for this exploratory analyses in this early phase clinical trial is to allow further investigation of a biologically interesting treatment which may have not hit a statistical boundary. The conclusions from the trial will be discussed with the DMC and reported with their independent guidance and recommendations.

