### OUTCOME DATA

| Tumour measures
N
Mean (sd)
Range | Baseline | 4-week | 12-week |
|--------------------------------------------|----------|--------|---------|
| ACTIVE                                     |          |        |         |
| Volume                                     |          |        |         |
| Surface Area                               |          |        |         |
| Height                                     |          |        |         |
| PLACEBO                                    |          |        |         |
| Volume                                     |          |        |         |
| Surface Area                               |          |        |         |
| Height                                     |          |        |         |

| VOLUME (cm  ) | Active |      |        | Placebo |      |        | Overall |      |        |
|---------------------------|--------|------|--------|---------|------|--------|---------|------|--------|
|                           | n      | mean | 95% CI | n       | mean | 95% CI | n       | mean | 95% CI |
| Baseline                  |        |      |        |         |      |        |         |      |        |
| Week 4 % change           |        |      |        |         |      |        |         |      |        |
| Week 12 % change          |        |      |        |         |      |        |         |      |        |

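### The protocol promises the median and inter-quartile range for change in tumour volume, but the SAP reports only the mean percentage change, so the protocol's summary would not be produced

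*Combined protocol and SAP*

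**What the plan says.** Change in volume is the first-listed secondary outcome of cohort 2 in Protocol 4.2: "Change in tumour volume from baseline (pre-randomisation) to 12 weeks". The protocol's analysis text for cohort 2 (section 14.1, subsection numbered 2.1.2) names this variable when it sets the summary measure: "Continuous measurements (including change in tumour volume from baseline) will be summarised and reported as medians and ranges (inter-quartile ranges"). It does not say whether the change is absolute or percentage.

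SAP 8.2.2.1 sets a different measure: "Tumour-level change in volume at 4 and 12 weeks will be reported as mean percentage change (with 95% Confidence interval) by randomised treatment group". For the check on initial tumour size it repeats the choice: "the mean percentage change from baseline to 4 weeks and baseline to 12 weeks will be reported by baseline tumour diameter categories". The matching Appendix 3 tables follow suit. The volume table has a row labelled "Week 12 % change" with columns for n, mean and 95% CI, and the tumour kinetics table gives the mean percentage change by diameter quartile. No median or IQR of volume change appears in the SAP.

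Other parts of the SAP bear on the point. Section 8.2.2.1 adds a plot of individual tumours: "Graphical representation of percentage change in tumour volume from baseline to 12 weeks will be in the form of a waterfall plot (Appendix 3"). Section 8.4 says that the decision at the end of Phase 2a is "predominantly based on the response rate and critical number of responses observed in the treatment group".

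**The concern.** Protocol 14.1 requires all analysis to follow the SAP. Where the SAP drops a summary that the protocol names, that summary will not be produced, and the SAP gives no reason for the change. Elsewhere the SAP uses the median and IQR freely: for Draize scores, compliance and baseline tumour diameter. For DLQI it gives both mean and median.

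The choice is not neutral. A percentage change cannot fall below -100% but has no ceiling, and its denominator is a measured volume of a small tumour (Protocol 8.3: ideally under 1 cm in diameter). A mean of such ratios and a median can tell different stories about the typical tumour. At stake are the arm-level figures for this outcome and possibly the table by initial size.

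**Working it through.** **The plan's own design figure.** Protocol 14.2 takes p0 = 5% and p1 = 15% and says that "75 tumours recruited in the experimental arm would provide evidence of a minimum level of efficacy of approximately 15"%, with a type I error of 3.4% and a type II error of 10.8%. The critical number is held in a separate document. By exact binomial calculation a threshold of 8 responses in 75 reproduces the stated errors:

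- P(X ≥ 8 | 75, 0.05) = 0.0336
- P(X ≤ 7 | 75, 0.15) = 0.1082

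These rest on the response proportion alone. Neither document gives a design figure, SD or distribution for volume change.

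**Model for the gap between mean and median (an assumption).** Let each visit's volume carry an independent log-normal error with coefficient of variation CV, so the log-scale variance per visit is ln(1 + CV²). Let the true 12-week volume be k times baseline. The log of the measured ratio then has variance s² = 2 ln(1 + CV²), and:

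- median % change = 100(k − 1)
- mean % change = 100(k·exp(s²/2) − 1) = 100(k(1 + CV²) − 1)
- with no true change, P(fall of at least 30%) = Φ(ln 0.7 / s)

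The median is 0% when k = 1 and −15% when k = 0.85, whatever the CV. The other results are:

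| CV | Mean, no change | Mean, true 15% shrinkage | Difference (points) | Falls of ≥30% from error alone |
|---|---|---|---|---|
| 10% | +1.0% | −14.2% | −15.2 | 0.6% |
| 20% | +4.0% | −11.6% | −15.6 | 10.1% |
| 30% | +9.0% | −7.4% | −16.4 | 19.5% |
| 40% | +16.0% | −1.4% | −17.4 | 25.6% |

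At CV 30% with no change, the SD of the percentage change is 100 × 1.09 × √(1.09² − 1) ≈ 47 points. With 75 tumours treated as independent, the standard error is 47.2/√75 ≈ 5.45, so the 9-point shift is about 1.65 nominal standard errors.

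**Calibration to the plan's placebo rate.** If 5% of unchanged tumours show a fall of at least 30%, then s = ln 0.7 / (−1.645) = 0.217. The mean is 100(exp(0.217²/2) − 1) = +2.4% against a median of 0%. The same s with a 15% response rate gives a median of −12.4% and a mean of −10.3%, a gap of about 2 points.

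**Reverse case.** Suppose 15% of tumours vanish (−100%) and the rest scatter around no change with log-SD 0.10. The mean is 0.15 × (−100) + 0.85 × 0.5 ≈ −14.6%. The median is −2.2% and the skewness is −1.7. Here the median understates what happened.

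**The case against.** The case for leaving the SAP alone is that the mismatch has little consequence. The analysis is exploratory. The primary outcome and the go/no-go rule use response counts, which extreme values of the mean cannot move. The waterfall plot shows every tumour at 12 weeks, SAP 8.3 tabulates alternative response cut-offs, and SAP 8.2.2.3 models volume with baseline as a covariate. SAP 8.1.2 averages three readings per visit, and Protocol 13.2 describes the imaging as sensitive and reproducible, so a CV of 30 or 40% may be pessimistic. Those CVs also imply that error alone would produce about 20 to 26% responses, four to five times the 5% placebo rate. The SAP was written for Protocol V2.1 and the protocol supplied is 3.0, so the texts may once have agreed.

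Most of this stands and limits the size of the point. Three things remain. The two documents still disagree. Protocol 14.2 offers its rates as an exemplar, so they are weak evidence on measurement spread. The waterfall plot covers week 12 only and does not give the median and IQR.

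A reader might go further and infer that the mean hides a real reduction. The documents do not support that. In the model above both arms are inflated together, and the difference between them is never smaller than the true 15 points. A reader might also take right skew, or a distortion worst in the smallest-diameter quartile, as established. The documents give neither a distribution nor any error by tumour size, and the reverse case shows left skew is possible.

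**Conclusion.** The conflict between the protocol and the SAP is certain, because it is in the text: the protocol's summary of a named secondary outcome would not be produced. The numerical consequence is conditional. Under the log-normal assumption the mean exceeds the median by 1 to 16 points for CVs of 10 to 40% with no true change, and by about 2 points if the 5% placebo response is taken as a guide. The gap can run the other way if a minority of tumours disappear, and a response in a minority (p1 about 15%) is what the design looks for.

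The point therefore bears on the arm-level figures for change. It bears on the diameter-quartile table only if relative error varies with tumour size, which the documents do not say. It does not touch the between-arm contrast, the response outcome or the decision rule. Nor does it justify replacing the mean with the median: each can miss something that the other shows, so both should be reported.

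**What to change.** Align the two documents before the Phase 2a data are analysed by arm. In SAP 8.2.2.1, and in the Appendix 3 tables for volume change and for diameter quartiles:

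- Report the median (IQR, range) of change by arm at 4 and 12 weeks, beside the mean percentage change.
- State whether the change is absolute or percentage, or give both. The protocol is silent on this.
- Compute any confidence interval for the change with the patient as the resampling unit, because tumours are clustered within patients.

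This needs only wording and table edits and no new data. The cost is slightly longer tables and possibly wider intervals. The sample size and the stated error rates do not change.
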